## Abstract

**Background:**

Non - pharmacological management of migraine, tension-type headache (TTH), and cervicogenic headache (CGH) may include spinal manual therapy and exercise. Mulligan Manual Therapy (MMT) utilizes a protocol of headache elimination procedures to manage headache parameters and associated disability, but has only been evaluated in CGH. There is little evidence for its effectiveness in migraine and TTH. This study aims to determine the effectiveness of MMT and exercise over exercise and placebo in the management of migraine, TTH, and CGH.

**Methods:**

This pragmatic trial is designed as a prospective, three-armed randomised controlled trial in a clinical setting provided at a general hospital physiotherapy department. Two hundred ninety-seven participants with a diagnosis of migraine, TTH or CGH based on published headache classification guidelines will be included. An assessor blind to group allocation will measure outcomes pre-and post-intervention as well as 3 and 6 months after commencement of treatment. Participants will be allocated to one of the three groups: MMT and exercise; placebo and exercise; and exercise alone. The primary outcome measure is headache frequency. Secondary outcome measures are headache duration and intensity, medication intake, pressure pain threshold (PPT), range of motion recorded with the flexion rotation test, and headache disability recorded with Headache Activities of Daily Living Index (HADLI). The intention-to-treat principle will be followed for statistical analysis. Between groups differences for all outcome measures at baseline and at reassessment points and 95% confidence intervals will be calculated using a mixed model ANOVA. Post hoc tests will be conducted to identify any significant difference between groups and over time.

**Discussion:**

This pragmatic study will provide evidence for the effectiveness of MMT when compared with a placebo intervention and exercise on headache frequency, intensity, and disability. Limitations are that baseline evaluation of headache parameters may be affected by recall bias. External validity will be limited to the population with a minimum 1-year history of headache. The HADLI is not yet extensively evaluated for its psychometric properties and association between PPT and headache parameters is lacking. Performance bias is inevitable as a single therapist will be delivering all interventions.

**Trial registration:**

The trial was registered prospectively under the Clinical Trial Registry India (Registration number: CTRI/2019/06/019506, dated on 03/06/2019). .

## Background

Headache is one of the most common disorders globally, with a potential for major disability. Migraine, tension-type headache (TTH), and cervicogenic headache (CGH) are common types of headache which negatively impact on quality of life, work activities, and family life posing a direct or indirect economic burden on society [1]. The global 1-year prevalence of primary headache in adults is 47% [2] with a lower but still substantial prevalence for specific headache disorders. The 1-year prevalence for migraine, TTH, and CGH in adults was documented as 15%, 21% [3], and 4% respectively [4].

Even though well defined in the third edition of the International Classification for Headache Disorders (ICHD) 2018 [5], headache diagnosis can be difficult due to the overlap of symptoms between migraine, TTH, and CGH [6, 7]. Moreover, in clinical practice, multiple headache forms may co-exist in up to 55% of cases [8]. This may explain the uncertainty in the initial diagnosis and subsequent shift in headache categorization that occurs in 40% of cases at subsequent follow-up [9]. Thus it is important to identify the predominant type of headache before planning management, for optimum patient care [10] .

The non-pharmacological management of common headache types can include physiotherapy [11]. This may consist of exercise and spinal manual therapy, the latter of which is often provided due to the presence of neck pain in these patients [12]. Neck pain is characteristic of CGH [5] but is also very common in people who suffer from migraine and TTH [13]. In migraine, neck pain is more prevalent than nausea [14] and is positively associated with headache frequency and increases overall headache related disability [15, 16].

It has been thought that neck pain occurring with headache could be due to cervical articular impairment [16, 17] or poor motor control of neck muscles [18, 19]. In contrast, neck pain may also be a symptom of headache which may be unrelated to musculoskeletal issues [20]. Various physical examination tests have been described to identify musculoskeletal dysfunction in headache which can guide non-pharmacological management [21]. However, the evidence regarding the importance of these clinical tests and therefore musculoskeletal dysfunction in headache diagnosis is poor [22].

Various systematic reviews favor the use of manual therapy as a part of non-pharmacological management of migraine [23, 24], TTH [25, 26], and CGH [27, 28]. It has been thought that manual therapy may modify identified articular dysfunction, particularly in the upper cervical spine, as well as improve muscle function and motor control.

In addition to postulated biomechanical effects, manual therapy has been shown to reduce the sensitivity of the trigeminocervical nucleus which is known to be a factor in headache pathophysiology [29]. For example, headache reproduction and resolution following manual palpation of the upper cervical spine in patients with primary headache [29, 30] indicates that manual therapy has the capacity to modulate the sensitivity of this nucleus.

Sensitization of the trigeminocervical nucleus appears to be a common feature in migraine, TTH and CGH [31]. Although such sensitization may have arisen through different means in each of the headache forms, desensitization of this nucleus by manual therapy and exercise may theoretically be a viable treatment option [12].

Mulligan manual therapy (MMT) is a relatively new concept that utilises pain-free low-velocity joint mobilisation techniques that can include an active movement component [32]. In this concept, pain-free sustained manual force is applied to the upper cervical spine in an attempt to modify headache or increase upper cervical spine mobility. If successful the technique becomes the treatment. If not then a new technique is trialled until all techniques are exhausted. The MMT protocol in headache management is essentially a symptom and impairment elimination approach and is indicated only if a substantial headache reduction and/or improvement in range of motion occurs as a result of the applied technique. Previous research of MMT has focused mainly on CGH [33]. The effects of such an approach on other headache forms have been reported in a case study [34] of a patient with features of migraine, but not in TTH and not in a formal RCT. Thus there is scope to explore the comparative effectiveness of MMT in the management of CGH, migraine, and TTH.

This paper aims to report the study protocol which will be used to investigate the short and mid-term effectiveness of MMT and exercise on headache frequency, intensity, disability, and duration as well as medication intake, upper cervical rotation range of motion, PPT and patient satisfaction compared with placebo and exercise and exercise alone in the management of migraine, TTH, and CGH. The objective is to investigate whether MMT with exercise is more effective than placebo MMT with exercise or exercise alone. Our primary hypothesis is that there will be a 50% reduction in headache frequency in the experimental group (MMT with exercise) and recovery is greater than that seen in the 2 control groups (placebo MMT with exercise and exercise alone).

## Methods/ design

Approval and registration of the study is confirmed. The design of this clinical trial follows the recommendations of the SPIRIT guidelines (2013) [35].

This is an assessor blind pragmatic randomized clinical trial with three parallel groups (MMT + exercise, placebo + exercise, and exercise alone) based on SPIRIT guide lines (2013) [35]. A chart indicating the flow of participants through the study is shown in Fig. 1.

**Fig. 1 Fig1:**
[figure not shown]
Flow chart of the study process based on SPIRIT guidelines (2013)

The study will be conducted at the physiotherapy department of Smt. Kashibai Navale Medical College and General Hospital, Maharashtra, India. This hospital is a multispecialty general hospital. Ethical approval was obtained from the ethical committee of the Smt. Kashibai Navale College of Physiotherapy (Approval number: SKNCOPT/IEC/2019/208) and institutional review board of Sancheti Institute for Orthopedic and Rehabilitation, Pune (Approval number: IRB-SIOR/ Agenda 049). Both committees are responsible for ethics and data monitoring throughout the trial. The trial was registered prospectively under the Clinical Trial Registry India (Registration number: CTRI/2019/06/019506, dated 03/06/2019).

### Eligibility criteria

Consecutive participants with episodic migraine, episodic TTH and CGH referred to the physiotherapy outpatient department by the hospital medical department will be recruited into this trial. A diagnosis of episodic migraine, episodic TTH and CGH will be made by the primary investigator under the guidance of a medical practitioner as per the ICHD -3 [5]. Episodic TTH is at least 10 episodes of headache occurring on 1–14 days/month on average for > 3 months (≥12 and < 180 days/year) and lasting from 30 min to 7 days. Episodic migraine is that which occurs on less than 15 days per month for at least 3 months [5].

Participants will be included if they fulfil the following inclusion criteria: age more than 18 years and less than 60 years, pain intensity > 6 on a 10 cm visual analogue scale at the time of presentation (to balance headache severity across different headache groups), a minimum 1-year history of headache with a minimum mean frequency of 1 per week. This frequency was chosen to enable effective monitoring of outcome, in particular with respect to treatment intervention. Less frequent headache would make it difficult to monitor progress. An additional criterion is hypomobility of the upper cervical spine (C0–3) on manual examination. Manual examination has been shown to be reliable when used in the upper cervical spine [36], and has been used in previous studies exploring the effectiveness of manual therapy for headache [37–40]. By way of standardization, an upper cervical spine joint is classified as impaired if moderate or marked tissue resistance is perceived along with local or referred pain of > 2 on a 0–10 cm visual analogue scale on palpation [41]. A further criterion is the reproduction of headache on palpation of the upper cervical spine (C0–3) [29].

Participants will be excluded if their headache diagnosis is other than, migraine, TTH or CGH. In addition, exclusion criteria are instability of the upper cervical spine, evidence of cervical arterial insufficiency observed during clinical testing, history of vertigo or dizziness, rheumatoid arthritis, ankylosing spondylosis, cervical spine fractures, pregnancy, cognitive compromise, and any other contraindications to manual therapy.

### Procedures

Participants will be provided with an information sheet outlining the study protocol including duration of commitment, intervention, benefits and harms of the treatment, voluntary participation, right to withdraw, as well as confidentiality of data. It will be explained that no compensation will be given if any adverse event occurs and study findings may be published but without revealing participants identity.

Those willing to participate will be enrolled and asked to provide signed written informed consent with the right to withdraw at any time. After recruitment, at initial assessment, a qualified therapist will explain the study procedures and collect demographic data. Confidentiality will be maintained throughout the trial.

Participants will then be randomly and equally allocated to one of three groups: MMT plus exercise; placebo plus exercise; or exercise alone by stratified randomization based on the type of headache. Randomization will be achieved using a computer-generated sequence received in advance from an independent statistician and will be hidden in sequentially numbered opaque sealed envelopes by a research assistant. All participants will be asked to not reveal their group identity and are advised to continue with their regular medical management. Any change in the protocol will be communicated with the ethics committee and if approved appropriate changes will be made in the Clinical Trial Registry.

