### Statistical methods

The sample size for this study was calculated based on the primary outcome of headache frequency. According to the International Headache Society guidelines (2018), a 50% reduction in headache frequency is considered a clinically significant difference. A sample size of 297 participants will be required for the study based on a priori power analysis with a power of 0.8 and an alpha of 0.05 assuming 10% drop-outs.

All data entry will be carried out by research assistants who will be blind to treatment allocation. The final trial dataset will be accessible to all investigators and a statistician. Data will be stored with the principal investigator. Descriptive statistics will be performed to examine baseline parameters and demographic data. Demographic data will include age, gender, symptom duration, occupation, height, and weight. Baseline parameters will include the headache frequency, intensity, duration, medication intake, PPT, HADLI score, and FRT range of motion. Parametric tests will be used for normal distributions and ratio level data. Between groups differences for the primary and secondary outcome measures at baseline and at reassessment points and 95% confidence intervals will be calculated using mixed ANOVA. Post hoc tests will be conducted to identify any significant difference between groups and over the time. The intention-to-treat principle will be used if loss of follow up is not more than 10%. Non-parametric tests will be applied for non-normal distributions and ordinal level data.

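### Randomisation is stratified by headache type, but the stated mixed ANOVA and its contrasts omit headache type, which can make the between-arm intervals at each visit too wide

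*Protocol article*

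**What the plan says.** **Allocation.** Under Procedures, "Participants will then be randomly and equally allocated to one of three groups", the third being "exercise alone by stratified randomization based on the type of headache". The strata are migraine, TTH and CGH.

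**Aim.** The last paragraph of the Background sets out to study MMT and exercise "compared with placebo and exercise and exercise alone in the management of migraine, TTH, and CGH". Its primary hypothesis compares the arms overall. Earlier in the Background the authors write that "there is scope to explore the comparative effectiveness of MMT in the management of CGH, migraine, and TTH".

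**Analysis.** Under Statistical methods, between-group differences for primary and secondary outcomes "at baseline and at reassessment points and 95% confidence intervals will be calculated using mixed ANOVA". Then: "Post hoc tests will be conducted to identify any significant difference between groups and over the time". The abstract describes the same model. Headache type is not named as a factor, a covariate or a subgroup. It is also absent from the descriptive variables: "Demographic data will include age, gender, symptom duration, occupation, height, and weight", followed by a list of baseline outcome values.

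**The concern.** Stratified allocation balances headache type across arms, so differences between types contribute almost nothing to the treatment difference. The standard error of an unadjusted between-arm difference at a visit still counts those differences as noise. The reported uncertainty then exceeds the real uncertainty, and the precision that stratification was meant to buy is not collected.

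The second issue is interpretation. The aim names three disorders, and the abstract says that MMT has so far been evaluated only in CGH. The stated contrasts give no estimate by type, so a reader of the results could not see whether the three disorders responded alike.

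**Working it through.** **The plan's own figure.** The total of 297 (power 0.8, alpha 0.05, 10% drop-out) cannot be reproduced, because the article gives no SD, between-arm difference, responder rates or sidedness. Working backwards:

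- 270 × 1.1 = 297, that is, 90 per arm before inflation. (267 / 0.9 = 296.7, rounded up to 297, would give 89 per arm.)
- With 90 per arm, two-sided 0.05 and power 0.80, the detectable difference is (1.960 + 0.842) × √(2/90) = 0.418 SD.

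This 0.42 SD is back-solved. The protocol does not state it.

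**Loss of precision at a single visit.** Let R² be the share of outcome variance due to headache type. It is an assumption, ranged here from 0 to 0.30.

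- Unadjusted over adjusted interval width = 1/√(1 − R²)
- True type I error of the unadjusted test = 2[1 − Φ(1.96/√(1 − R²))]
- Unadjusted power = Φ((2.80 − 1.96)/√(1 − R²)), where 2.80 = 0.418/√(2/90)
- Adjusted power = Φ(2.80/√(1 − R²) − 1.96)

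| R² | Interval too wide by | True type I error | Power unadjusted | Power adjusted |
|---|---|---|---|---|
| 0 | 0% | 0.050 | 0.80 | 0.80 |
| 0.05 | 2.6% | 0.044 | 0.81 | 0.82 |
| 0.10 | 5.4% | 0.039 | 0.81 | 0.84 |
| 0.20 | 11.8% | 0.028 | 0.83 | 0.88 |
| 0.30 | 19.5% | 0.019 | 0.84 | 0.92 |

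A simulation with 90 completers per arm and 30 per arm and type (40,000 runs per row) agrees. Unadjusted type I error was 0.051, 0.044, 0.039, 0.028 and 0.021. With type in the model it was 0.049 to 0.051 throughout.

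**Group-by-time test.** This interaction is tested against within-participant error, from which a type difference that is constant over visits has already been removed. In a simulation with four visits and such a constant effect (4,000 runs), type I error was 0.056, 0.049, 0.046 and 0.051 at R² = 0, 0.10, 0.20 and 0.30. The test is not conservative, so the table does not apply to it. Nor does it apply to change-from-baseline contrasts when the type effect is constant.

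**Information by type.** Equal thirds are assumed, so 30 completers per arm and type.

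- Power within one type at 0.418 SD: Φ(0.418/√(2/30) − 1.96) = Φ(−0.34) = 0.37.
- Half-width of the 95% interval: 1.96 × √(2/30) = 0.51 SD, against 1.96 × √(2/90) = 0.29 SD pooled.
- Illustration: true effects of 0, 0.63 and 0.63 SD average 0.42 SD. The pooled comparison of two arms keeps power 0.80 although one type gains nothing. A 2-df treatment-by-type interaction test detects this with power of about 0.40.

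**The case against.** **Silence is not exclusion.** The article is condensed, and a statistical analysis plan may already contain the stratum. That is fair, and if so the remedy is only to align the text. But the article names its model, its contrasts and its baseline variables, and headache type is in none of them. Followed as written, the analysis does not match the randomisation. The word groups in the analysis text most naturally means the three arms, although Eligibility criteria and Discussion also use it for diagnoses.

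**The size is unknown and may be negligible.** This stands. All participants have at least one headache per week, and migraine and TTH are both held below 15 days per month, which limits the spread between types. No such limit is stated for CGH, so R² need not be zero either.

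**The error is on the safe side.** This also stands. Unadjusted power stays at or above 0.80 in every row of the table.

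**Stronger readings.** A reader might infer that the planned intervals are simply wrong. The documents support only that they are too wide at a visit if type is prognostic. A reader might also infer that a pooled result will be claimed for each disorder. The objective and primary hypothesis compare arms overall, the remark on comparative effectiveness is background rationale, and no type-specific claim is announced. Finally, a reader might apply the quoted prevalences (15%, 21% and 4%) and conclude that CGH will supply only about 30 participants (297 × 4/40 = 29.7). Those are population figures. Recruitment is by referral to a physiotherapy department, with upper cervical signs required, so they do not predict the case mix.

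**Conclusion.** The point holds in a limited form. The stated analysis leaves out the stratification factor. For the between-arm differences and intervals at each reassessment this costs between nothing and about 20% in interval width, with type I error between 0.050 and 0.019, as the variance share of headache type goes from 0 to 30%. That share is an assumption. At the back-solved 0.42 SD, the power forgone runs from 0 to 0.075 (0.918 − 0.843). There is no false-positive inflation and no effect on the group-by-time test when type differences are constant over time.

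The lack of by-type estimates is a gap between the three disorders named in the aim and the contrasts listed. It does not invalidate the pooled comparison. With power of about 0.37 within a type, under equal thirds and the back-solved effect, by-type results could only be exploratory.

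**What to change.** 1. Add headache type, as the stratum used at randomisation, as a fixed factor in the models for the primary and all secondary outcomes, and include it in the baseline description.
2. Pre-specify one treatment-by-type interaction for the primary outcome, and report the treatment difference with its 95% interval for each type. Label both exploratory and low-powered.
3. State that the confirmatory conclusion concerns the pooled population and that no efficacy claim for a single type rests on a within-type p-value.
4. Say explicitly that groups in the analysis text means the treatment arms.

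The cost is one model term and a few sentences. The variable is already recorded for randomisation, and neither the sample size nor any study procedure changes. If an analysis plan already does this, a sentence in the protocol saying so is enough.

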### Interventions

Each subject will receive 6 treatment sessions spread over 4 consecutive weeks and each treatment session will not extend beyond 30 min. A principal investigator will perform all the interventions. The principal investigator is a physiotherapist with a Masters degree in musculoskeletal physiotherapy with 15 years of clinical experience who has undertaken the highest level of training in MMT.

All participants will be informed that their designated intervention has been shown to improve headache symptoms. Treatment will cease if the subject withdraws consent, has an increase in pain or discomfort due to the treatment, or develops any contra-indication during the intervention period. Additionally subjects will be withdrawn if they receive any other physiotherapy program including massage, manual therapy or chiropractic treatment to the neck or shoulder region. All participants will be requested to avoid any forms of manual therapy or massage until the final evaluation at 6 months.

All participants will receive the following structured exercise programme encompassing conventional cervical flexion loading exercise [42], upper quarter low load endurance training, stretching, and generalized mobility exercises [43]. All exercises will be supervised during each session and exercise parameters will be adjusted if required but without any modifications in the type of exercise.

Exercises will be performed in the following sequence. 1. A conventional cervical flexion loading exercise [42] is performed with the subject in a supine position with the knees bent and neutral head/neck position. The head lift exercise will be taught ensuring that the craniocervical spine will be maintained in a neutral position while lifting the head from the supporting surface [42]. 2. Scapular retraction in prone with the subjects arms by their side, performed against gravity resistance. For the first 2 weeks, 2 sets of 5–10 repetitions with a 10 s hold of the above two exercises will be performed, building slowly to 3 sets of 15 repetitions with 10–15 s hold over the next 4 weeks. 3. Passive static self-stretching exercises for the upper trapezius, levator scapulae, scalene, and sternocleidomastoid muscles will be delivered only if tightness is perceived on assessment. Stretching will be maintained for 30 s with 3 repetitions given to each tight muscle. 4. Active mobility exercises of the neck for flexion, extension, side flexion and rotation to either side will be included [29]. Two sets of 10 repetitions will be performed. Participants will be advised to undertake similar exercise at home, unsupervised, once a day. Participants will be asked to maintain an exercise diary to monitor compliance.

The group receiving MMT and exercise in addition to the exercise program will receive the MMT protocol for headache. MMT will be delivered at the discretion of the therapist, based on the initial and progressive assessment of the participant’s cervical joint dysfunction and headache presentation. The protocol is as follows (Fig. 2):

